### Who will take informed consent? {26a}

At an in-person meeting, the investigator who performs the assessments will explain the study details and clarify any questions. Then, the participant will be asked to sign the consent form. It consists of the details, such as the title of the study, names of investigators, registered information, research background, how the study was to be conducted, what the participants should do in the study, treatment plans, and obligations.

### Additional consent provisions for collection and use of participant data and biological specimens {26b}

Not applicable.

## Interventions

### Explanation for the choice of comparators {6b}

After obtaining written informed consent, baseline measurements will be performed. Participants will then be randomized to either active control or experimental group (1:1 ratio) using a stratified block allocation with stratification factors being gender (male or female) and with a block size of four. Randomization will be done at the Iran University Medical Sciences by an independent investigator using WinPepi (version 11.65). The randomization schedule will be known only to 1 investigator who is not involved in recruiting participants. The randomization will be concealed from patients and the other investigators involved in patient assessments, treatments, and analyses.

### Intervention description {11a}

All interventions are performed by two expert and trained physiotherapists with 6 years of work experience in the treatment of LBP patients. The intervention lasts six weeks and each group will receive 12 sessions of physiotherapy.

#### Experimental group

Patients in the experimental group will receive multidimensional physiotherapy include psychoeducation based on cognitive behavioral therapy (CBT), lifestyle education, graded exposure, postural correction exercise, and electrotherapy. Twelve 30-min psychoeducation sessions consist of the following sessions:
Psychoeducation on pain based on the book “Explain Pain” [32] and set the goal of treatment (3 sessions);Anxiety management: The goal of this session is to identify signs and symptoms of anxiety and to learn coping skills to improve the individual’s functioning in the area of anxiety.Interpersonal conflict management: The goal of this session is to have individuals learn how to manage conflict more effectively and increase effective skill use in relationships.Problem-solving training: The goal of this session is to promote problem-solving strategies in complex situations and with others.Coping strategy training: The goal of this session is to deliver insight and information about coping strategies for chronic pain and to learn coping skills for improving patient functioning in the areas of common defense mechanisms.Pain flare-ups management: This session is run to identify triggering events and typical reactions and promote coping skills with the fear and avoidance conditioning.Medication abuse management: This session is held to learn coping skills to improve the individual’s functioning in accepting reality and learn coping skills to improve the individual’s functioning in chemical abuse.Enhancing one’s ability to cope with labeling and stigma: The goal of this session is to give insight and understanding into the effects of stigma and learn coping skills to improve the individual’s ability to cope effectively with stigma.Empowering one to create a daily sleep routine: The goal of this session is to learn coping skills to improve the individual’s functioning in the areas of building and maintaining healthy sleep patterns.Training relaxation techniques [33].

Patients will also receive recommendations for lifestyle modifications, such as encouraging active living and a gradual increase in activity levels, improving the work environment, and training on how to perform daily and work activities correctly. Other treatments include postural correction and training of the necessary exercises, as well as the gradual initiation of movements and activities that the patient is afraid of, and by asking the patient to perform hierarchical activities that he or she fears. The first step is to identify the movements that the patient is afraid of. The exercise begins with a movement that the patient has the least fear of, and that movement begins with the simplest state and the lowest level with the patient least feared, and gradually becomes more difficult [34, 35]. All of these are taught to the patient in each practice session. The patient will also be asked to repeat the practice of each session at home once a day. Electrotherapy, including 20 min of transcutaneous electrical nerve stimulation (TENS) at 100 Hz in the lumbar region where the patient reports the most pain, will also be done. The intensity of TENS is regulated by the patient. Surface heat will be placed in the lumbar area by Hot Pack at the same time as TENS. Ultrasound with a frequency of 1 MHz and intensity of 1.2 W/cm^2^ will be performed using a 5-cm square applicator on the paravertebral muscle where the patient reports the most pain, for 5 min. The treatment in this group is twelve sessions and will be performed twice a week.

#### Active control group

For patients in the active control group, treatment will include education, trunk general exercises, and electrotherapy. Education in this group includes an explanation of the basic biomechanical anatomy of the spine, common causes of spinal pain, pain processing, ergonomic advice on how to perform daily activities, and postures (such as sitting, standing, moving objects, etc.), and training for postural correction exercises. General trunk exercise will focus on abdominal and paraspinal muscles to improve blood flow, mobility, strength, and endurance in each session, and the patient will be asked to perform exercises in each session [36]. The intensity and type of exercise will progress toward functional training. The patient is also asked to do exercise at home once a day. Electrotherapy, including 20 min of skin electrical nerve stimulation (TENS) at 100 Hz in the lumbar region where the patient reports the most pain, will also be done. The intensity of TENS is regulated by the patient. Surface heat will be placed in the lumbar area by Hot Pack at the same time as TENS. Ultrasound with a frequency of 1 MHz and intensity of 1.2 W/cm^2^ will be performed using a 5-cm square applicator on the paravertebral muscle where the patient reports the most pain, for 5 min. The treatment in this group is twelve sessions and will be performed twice a week.

### Criteria for discontinuing or modifying allocated interventions {11b}

Not applicable

### Strategies to improve adherence to interventions {11c}

Not applicable

### Relevant concomitant care permitted or prohibited during the trial {11d}

Relevant concomitant care and interventions are prohibited during the trial.

### Provisions for post-trial care {30}

No physical or psychological damage has been predicted in this study; however, any possible problem, either physical or mental, which arises during the research, due to the treatment will be reported to the Iran University of Medical Sciences ethics committee. The study team will give priority to unpaid examination and treatment according to the regulations of the Ethics Committee.

## Outcomes {12}

The pain will be the primary outcome. The secondary outcomes will include quality of life, fear avoidance beliefs, kinesiophobia, pain catastrophizing, disability, forward flexion ROM, and absolute and relative power of the frequency spectrum of EEG.

### Primary outcome

The pain will be assessed through a self-reported questionnaire. This questionnaire will be used for pain assessment at baseline, post-treatment, and at 1 and 4 months follow-up:
A Numerical Rating Scale (NRS) for pain ranging from 0 “no pain at all” to 10 “worst imaginable pain” (“How would you rate your low back pain, on average, over the last 3 days?”) [37].

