### Sample size {14}

Sample size calculations were performed with G*Power 3.1.9.4 (Düsseldorf, Germany) based on the therapy effects on pain and accounting for a 10% loss to follow-up after 4 months. Calculations were based on one-tailed testing with alpha set in 0.025, partial η2 = 0.04, and the desired power of 0.95. The allocation ratio (N2/N1) was defined as 1, resulting in 35 patients in the intervention group and 35 in the control group.

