## Statistical methods

### Statistical methods for primary and secondary outcomes {20a}

Data analysis will be performed using SPSS (version 22) and STATA (version 14.2). Baseline characteristics will be summarized with standard descriptive statistics. Categorical variables will be described with percent and counts. Continuous variables will be described with means and standard deviations. Statistical analysis of the primary and secondary outcomes will be based on the intention-to-treat principle including all randomized patients using an analysis of variance/covariance (ANOVA/ANCOVA). A model including baseline as continuous covariate and group as fixed factors will be used with using Bonferroni post hoc analyses and adjusting for differences in patients’ characteristics at baseline where appropriate will be done. Subgroup analysis of pain catastrophizing variable will be done. For all statistical tests, the significance level will be set at 0.05. Mean difference and standardize Mean difference and their 95% confidence intervals (Cohen’s *D*) will be calculated as are effect sizes.

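### Pain is the primary outcome at three post-baseline visits, but no primary visit or decision rule is named and the Bonferroni step has no stated family

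*Protocol article*

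**What the plan says.** All references are to the protocol article.

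- **Outcomes {12}**: "The pain will be the primary outcome". No time point is attached. The primary objective in Objectives {7} gives none either.
- **Primary outcome**: the 0–10 NRS, with "This questionnaire will be used for pain assessment at baseline, post-treatment, and at 1 and 4 months follow-up". That is three post-baseline measurements of equal standing.
- **Statistical methods {20a}**: "A model including baseline as continuous covariate and group as fixed factors will be used with using Bonferroni post hoc analyses". No time factor or group-by-time term is named. The same paragraph adds: "For all statistical tests, the significance level will be set at 0.05".
- **Sample size {14}**: "Calculations were based on one-tailed testing with alpha set in 0.025, partial η2 = 0.04, and the desired power of 0.95", and "The allocation ratio (N2/N1) was defined as 1, resulting in 35 patients in the intervention group and 35 in the control group". Four months appears in this section only through "accounting for a 10% loss to follow-up after 4 months".

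**The concern.** The primary question is whether multidimensional physiotherapy reduces pain more than usual physiotherapy. The article gives three occasions on which that can be tested and no rule for combining them. The visits also answer different questions: the effect at the end of treatment is not the same estimand as the effect that persists at 4 months.

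A model with baseline and group only, applied to an outcome measured three times after baseline, gives three group tests. If each is read at 0.05 and any one of them can support the claim, the type I error for the trial's main conclusion exceeds 5%, and the choice of visit can be made after the data are seen.

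The Bonferroni wording does not close this gap. A post hoc correction acts on pairwise contrasts among the levels of a factor. Group is the only factor named. It has two levels and so one contrast, and the correction changes nothing. Nothing in the text links it to the visits.

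**Working it through.** **1. Inputs**

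- From the article: three post-baseline visits; 0.05 for all tests; partial η² = 0.04; one-tailed α = 0.025 and power 0.95 for the sample size; 70 patients; 10% loss to follow-up.
- Assumed, because the article does not give them: the between-visit correlation ρ of the test statistics (taken as equal for all pairs of visits), two-sided testing at 0.05 in the analysis, and sphericity in step 2.

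**2. The plan's own figure, N = 70**

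Effect size: f = √(0.04/0.96) = 0.204.

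The figure is reproduced as a repeated-measures within–between interaction in the G*Power parameterisation, with 2 groups, m = 4 measurements, α = 0.025, assumed ρ = 0.5 and sphericity:

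- λ = f²·N·m/(1−ρ) = 0.04167 × 62 × 4/0.5 = 20.67
- df1 = (2−1)(4−1) = 3; df2 = (62−2)(4−1) = 180
- Power = 0.956. With equal arms, N = 60 gives 0.948, so 62 is the smallest even N that reaches 0.95.
- 62/0.9 = 68.9, so 69, and 70 for equal arms.

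Other designs tried with the same effect size do not give 70:

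| Design | N before dropout |
|---|---|
| Two means at one visit, d = 0.408, one-sided 0.025 | 312 |
| ANCOVA F test at one visit, α = 0.05 | 314 |
| ANCOVA F test at one visit, α = 0.025 | 366 |
| Between-group effect averaged over 4 measurements, ρ = 0.5, α = 0.025 | 230 |

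Of the designs tried with the stated α, only the group-by-time interaction fits. The analysis section does not contain that test, and its significance level is 0.05, not 0.025.

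**3. Family-wise error if each visit is tested at 0.05**

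Under independence: 1 − 0.95³ = 1 − 0.857 = 0.143. For correlated visits, 2 million draws of three equicorrelated standard normal statistics were used. The Bonferroni column uses 0.05/3 = 0.0167 per visit.

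| ρ | Any visit significant, two-sided 0.05 | Any visit falsely favouring the experimental arm (upper 0.025 each) | Two-sided, Bonferroni over visits |
|---|---|---|---|
| 0 | 14.3% | 7.3% | 4.9% |
| 0.3 | 13.7% | 6.8% | 4.8% |
| 0.5 | 12.5% | 6.3% | 4.5% |
| 0.7 | 10.9% | 5.5% | 3.9% |
| 0.8 | 9.8% | 4.9% | 3.5% |
| 0.9 | 8.4% | 4.2% | 3.0% |

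For one named visit the corresponding rates are 5% two-sided and 2.5% for a false claim of benefit. A single omnibus interaction test would have its nominal level, 0.05 or 0.025.

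**4. Power of a single-visit ANCOVA at the plan's effect size**

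Completers: 70 × 0.9 = 63. λ = f²·N = 0.04167 × 63 = 2.63, with df = 1 and 60.

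- α = 0.05: power about 36% (39% with all 70)
- α = 0.0167: power about 21% with 63 completers

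**The case against.** The strongest reply is that the article nowhere says each visit is tested separately without correction, or that any one significant visit counts as success. Since a Bonferroni step is pointless for two groups, its natural target might be the visits. The sample size also points to one longitudinal test, and an omnibus interaction followed by Bonferroni comparisons is a common design. On either reading the error rate is at most 5%.

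Much of this stands. A reader might infer that the plan carries a 10 to 14% false-positive rate as a settled fact. The document does not support that: it is the upper part of a range and depends on the Bonferroni step not covering the visits. It is also a two-sided rate that counts results favouring usual physiotherapy. A false claim of benefit is about 5 to 7%.

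The reply does not remove the defect. The interaction reading needs a correlation and a sphericity assumption that the article does not state, uses a different α, and has no counterpart in the stated model. The favourable reading of Bonferroni is a guess about an undefined family. The text is compatible with at least three primary tests and does not choose among them.

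Two further inferences should be resisted. First, 4 months is not a stated anchor for the sample size, since it appears there only as the horizon for loss to follow-up. Second, the slash between ANOVA and ANCOVA is not good evidence of a free choice between two tests, because the next sentence specifies a model with baseline as covariate.

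Nor is this only detail that an article leaves to an analysis plan. The article does state a primary outcome, a model and a significance level, and run as written these give three primary tests.

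**Conclusion.** The concern holds in a conditional form. No primary visit or decision rule is fixed for pain, and the family for the Bonferroni step is undefined. Depending on the reading, the two-sided family-wise error is at most 5% (Bonferroni over the three visits, or one omnibus test) or about 10 to 14% (uncorrected visits, ρ from 0.8 to 0; 8.4% at ρ = 0.9). For a false claim of benefit, the uncorrected rate is about 5 to 7%, against 2.5% for one visit. The correlation is an assumption throughout.

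The stated model and its 0.05 level also do not match the test that reproduces N = 70. Because this governs the trial's main claim and can be settled cheaply before results are seen, it should be corrected.

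**What to change.** In Primary outcome and in Statistical methods {20a}, do one of the following before any results are seen:

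1. Name one primary contrast: the baseline-adjusted (ANCOVA) between-group difference in NRS pain at one visit chosen by the sponsor, two-sided 0.05, with the other two visits secondary. Four months is a reasonable default, but the choice is the sponsor's.
2. Keep all three visits primary and state that the Bonferroni correction covers them, at 0.05/3 = 0.0167 each.

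In either case, state the family to which the Bonferroni step applies. Do not simply delete it, because it is the only multiplicity wording in the plan. Then reconcile the chosen test and its α with Sample size {14}, stating the test, the number of measurements, the assumed correlation and the sphericity assumption behind N = 70.

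**Cost.** The text change is a few sentences and adds no procedures. The sponsor can no longer claim success on any one of three visits at 0.05. The stated 95% power must also be restated: at the stated effect size a single-visit ANCOVA has about 36% power with 63 completers, or about 21% per visit at 0.0167. The fix does not create the 36%, which already applies to each visit under the model as written, but it makes it visible.

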### Secondary outcomes

#### Psychosocial correlates

Patients will complete some questionnaires at baseline, after 12 treatment sessions, and at 1- and 4-month follow-ups. The following standardized and reliable questionnaires (Persian version) will be used to measure psychological factors that may interfere with pain:
Self-reported pain catastrophizing based on the Pain Catastrophizing Scale. The Pain Catastrophizing Scale (PCS) will be included to assess catastrophic thinking about pain. It consists of 13 items describing different thoughts and feelings that individuals may have when experiencing pain. Items are scored on a 5-point scale, 0 “not at all” to 4 “all the time.” A general score and scores on 3 subscales (i.e., helplessness, magnification, and rumination) will be obtained; higher scores indicate more severe catastrophic thoughts about pain [38, 39].Self-reported kinesiophobia based on the Tampa scale of Kinesiophobia. The Tampa Scale for Kinesiophobia (TSK) is a 17-item questionnaire that will be used to measure the fear of(re) injury due to movement. Scores range from 17 to 68, with scores ≤ 37 suggesting low fear of movement and scores > 37 indicating high fear of movement. The TSK-Persian version that will be used in this study is shown reliable and valid [40, 41].Self-reported fear avoidance beliefs based on the Fear Avoidance Beliefs questionnaire. The Fear Avoidance Beliefs questionnaire (FABQ) is a 16-item self-reporting questionnaire evaluating patient’s attitudes and beliefs toward the effect of physical activity and work on their pain. The FABQ is divided into two subscales which are designed to assess beliefs about work and physical activity. The agreement of patients with each item will be scored by a 7-point Likert scale, ranging from 0 (completely disagree) to 6 (completely agree). Higher FABQ scores indicate higher fear-avoidance beliefs [42, 43].

#### Quality of Life

The 36 Health Status Survey (SF-36) will be used to assess functional status and well-being or quality of life. The SF-36 contains 8 dimensions (physical functioning, social functioning, physical role, emotional role, mental health, vitality, bodily pain, and general health perceptions). The overall value ranges from 0 to 100, with improvement as scores increase. The psychometric properties of the SF-36 are well-characterized in a wide variety of patient populations [44–46].

#### Disability

Self-reported disability based on the Oswestry Disability Index Questionnaire. The Oswestry Disability Index is currently considered for measuring the degree of disability in patients with low back pain. The questionnaire contains ten topics concerning the intensity of pain, lifting, ability to care for oneself, ability to walk, ability to sit, sexual function, ability to stand, social life, sleep quality, and ability to travel. Each question is scored on a scale of 0–5 with the first statement being zero and indicating the least amount of disability and the last statement is scored 5 indicating the most severe disability. The scores for all questions answered are summed and a higher score indicates greater disability [47, 48].

#### Forward flexion range of motion (ROM)

Forward flexion ROM will be measured by the third finger to ground distance by a meter.

#### Brain function

In this study, EEG will be recorded (bandwidth is 0.2–70 Hz, the impedance is less than 20 kHz, and the sampling rate is 512 Hz) with 64 channel amplifiers (EB Neuro, Italy) according to the international 10/20 system, from 19 Ag/AgCl surface electrodes and a diameter of 8 mm electrode sites distributed throughout the whole head of the participants. The 15 electrodes will be placed in Fp1, Fp2, F7, F3, Fz, F4, F8, T3, C3, Cz, C4, T4, T5, P3, Pz, P4, T6, O1, and O2. TCD will be performed in the above areas in the frequency range of delta, theta, alpha, beta, and gamma, and the relative and absolute power levels of each will be evaluated. A reference electrode is placed on the mastoid process and a ground electrode is placed on the Fpz region. To record vertical and horizontal electrooculogram, a pair of electrodes above and below the right eye and another pair are placed on either side of each eye. With the electrooculogram and the O1 and O2 electrodes, blinking and eye movement artifacts are controlled. EEG will be recorded under two conditions: while subjects rested with their eyes open for 3 min and while they will forward flexed in 20 s.

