The perception of pain is the result of a complex, dynamic system. The relationship between nociceptive information and pain is profoundly impressed by affective and cognitive factors. A specific region of the cortex that is responsible for pain processing has not yet been found; however, a complex network of brain regions known as a pain matrix has been identified. According to the neuromatrix theory of pain, chronic pain is considered a multidimensional experience and needs new forms of multidimensional treatment. The area of the brain involved in pain experience is a large and widespread network of neurons that consists of loops between the thalamus and cortex, as well as between the cortex and limbic system. These loops are not just for pain perception but also are involved in other sensory, motor, and cognitive functions [15, 16]. Functional MRI studies have shown that spontaneous back pain in CLBP patients does not activate the areas of the pain matrix typically seen during noxious stimulation, which supports the notion that chronic pain may not be caused by the nociceptive process [17].

Although growing knowledge exists on the peripheral and spinal neuronal mechanism of pain chronification processes, little is known about the accompanying neural mechanisms of chronic pain [18]. Recent studies have identified a relationship between chronic neurogenic pain and the presence of specific electroencephalography (EEG) pattern called thalamocortical dysrhythmia (TCD). TCD is characterized by a common oscillatory pattern in which resting-state alpha activity is replaced by cross-frequency coupling of low- and high-frequency oscillations. Despite many advances in the treatment of chronic pain, major challenges remain, and the main cause is the lack of precise diagnosis of the underlying cause of chronic pain. The somatosensory cortex and thalamocortical loop appear to be the best candidate for understanding chronic pain because these regions are most active in processing sensory information and have a strong role in processing pain [18–20].

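### No key EEG variable is named and the Bonferroni step has no stated scope, so up to 380 EEG comparisons per visit could be tested at 0.05 without error control

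*Protocol article*

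**What the plan says.** Outcomes {12} lists the EEG outcome among the secondary outcomes as part of "forward flexion ROM, and absolute and relative power of the frequency spectrum of EEG", with no key variable. The Brain function section lists 19 scalp sites by name and evaluates them "in the frequency range of delta, theta, alpha, beta, and gamma, and the relative and absolute power levels of each will be evaluated". It adds that "EEG will be recorded under two conditions": rest with eyes open, and forward flexion.

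Statistical methods {20a} covers EEG with the rest: "Statistical analysis of the primary and secondary outcomes will be based on the intention-to-treat principle", using ANOVA or ANCOVA. On the model it says: "A model including baseline as continuous covariate and group as fixed factors will be used with using Bonferroni post hoc analyses". On the threshold it says: "For all statistical tests, the significance level will be set at 0.05".

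The Background {6a} describes thalamocortical dysrhythmia as a pattern in which "resting-state alpha activity is replaced by cross-frequency coupling of low- and high-frequency oscillations". The Brain function section uses that label for an evaluation made up of band power alone.

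**The concern.** The EEG outcome is a grid of variables, and the protocol gives no rule for deciding which cell answers the brain-function question. With one threshold of 0.05 for all tests, and a correction not tied to the EEG family, some band at some site can reach significance by chance and be reported as an effect of treatment on the brain.

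This matters because the EEG spectrum is part of the study aim in the Abstract, brain function is a stated secondary objective, and the Discussion hopes that the trial will help refine practice guidelines. With 70 patients and no named contrast, a reader of the results could not tell a chance finding from a real one, nor a planned contrast from one chosen after the data were seen.

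**Working it through.** The protocol states no EEG test count and no familywise error rate, so there is no figure of its own to reproduce on this point.

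**Inputs from the protocol**

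- Bands: 5 (Brain function)
- Sites: 19 named (Brain function; the same section also gives the number 15, although 19 names follow)
- Power measures: 2, absolute and relative (Outcomes {12}; Brain function)
- Conditions: 2 (Brain function)
- Post-baseline visits: 3 by the general statements in the Abstract and Trial design {8}; the Brain function section gives no visits
- Threshold: 0.05 for all tests (Statistical methods {20a})

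**Step 1. Number of comparisons if each cell is tested**

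- One visit, one condition: 5 × 19 × 2 = 190
- One visit, both conditions: 190 × 2 = 380
- Three visits: 380 × 3 = 1,140
- With 15 sites: 5 × 15 × 2 × 2 = 300 per visit, and 300 × 3 = 900

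**Step 2. Expected false positives under no effect** (count × 0.05; this holds at any correlation)

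- 190 × 0.05 = 9.5
- 380 × 0.05 = 19
- 1,140 × 0.05 = 57
- With 15 sites: 300 × 0.05 = 15, and 900 × 0.05 = 45

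**Step 3. Chance of at least one false positive**

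Under independence this is 1 − 0.95^k: 0.99994 for k = 190, and above 0.9999 for 380 and 1,140.

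EEG cells are not independent, and the protocol gives no correlations, so the values below are assumptions. With one common correlation between all test statistics:

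| Assumed correlation | 380 tests | 1,140 tests |
|---|---|---|
| 0.5 | 0.97 | 0.9998 |
| 0.7 | 0.69 | 0.84 |
| 0.8 | 0.48 | 0.59 |
| 0.9 | 0.28 | 0.33 |
| 0.95 | 0.18 | 0.21 |

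With a structured correlation (simulation, 4,000 runs, 1,140 tests; sites / bands / measures, conditions and visits):

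- 0.8 / 0.5 / 0.7: 0.997
- 0.9 / 0.7 / 0.8: 0.91
- 0.95 / 0.8 / 0.9: 0.61

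Strong correlation makes false positives come in clusters. In the last case the median number falls to 3 while the expected number stays at 57. False findings are then less frequent, but when they occur they look like a consistent pattern over many sites.

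**Step 4. What the Bonferroni step could cover**

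- The two groups: one comparison, so nothing is corrected.
- The three visits, 0.05/3 per test: over 1,140 independent tests the chance of at least one false positive is still above 0.9999.
- The 19 sites, 0.05/19 per test: 0.95 over 1,140 independent tests.
- All EEG cells, 0.05/1,140 = 0.0000439 per test: at most 0.05.

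Only the last controls the EEG family, and nothing in the text points to it.

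**The case against.** The strongest reply is that the protocol never says each cell gets its own test. It says that power will be evaluated, which leaves room for averaging over sites or a joint model. That is correct: cell-by-cell testing is the natural reading, because sites, bands and both measures are listed and no averaging is mentioned, but it is not an explicit statement. The counts are therefore ceilings.

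The factor of three visits is weaker still. The pain and questionnaire sections give their own visits and the EEG section does not; the schedule figure (Fig. 2) is not reproduced in the text examined. The figure of 380 per visit is what the EEG section supports.

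A reader might infer that a false brain-function effect is all but certain. The documents do not support that. Neighbouring sites, two measures of one signal and repeated recordings on the same patients are likely to be strongly correlated, and under strong correlation the chance falls well below one.

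A reader might also infer that Bonferroni certainly corrects nothing. Its scope is undefined, and full coverage would control the family. The defensible criticism is that the scope is not stated and that the model, with two groups as its only factor, does not extend it to EEG variables.

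Nor does it follow that band power has no bearing on thalamocortical dysrhythmia. Loss of alpha is part of the described pattern, and the Discussion frames the aim as change in band spectra. What band power cannot show is the coupling.

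Finally, multiplicity detail for secondary outcomes is often left to an analysis plan, and one may exist. That answers a complaint about missing detail. It does not answer the point that this document itself fixes 0.05 for all tests and names a correction without a scope.

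**Conclusion.** The concern stands as a gap in error control for a secondary outcome. The stated rule, followed as it most naturally reads, gives up to 380 between-group EEG comparisons per visit with about 19 false positives expected under no effect. The three-visit figures, 1,140 and 57, apply only if EEG is recorded at every post-baseline visit.

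The chance of at least one false positive cannot be fixed without the correlations. Over the assumed common correlations from 0.5 to 0.95 it runs from 0.97 to 0.18 for one visit, so even the lowest value is more than three times 0.05 (0.18 / 0.05 = 3.6). These results assume separate two-sided tests and no Bonferroni coverage of the EEG family.

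Pain is the primary outcome and its conclusion is unaffected. The mismatch between the dysrhythmia label and the band-power measure is a lesser point about wording.

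**What to change.** In Outcomes {12} and Statistical methods {20a}, before the data are unblinded:

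- Name one or two key EEG contrasts. One example is resting relative alpha power averaged over fixed sites at post-treatment, which follows from the alpha change described in the Background. Any second band should be chosen and justified by the investigators, since the protocol states no hypothesis for a specific second band.
- Test the named contrasts with Holm at 0.05 overall. With two contrasts, the smaller p-value is compared with 0.025 and, if that is met, the larger with 0.05.
- Label all other band-by-site results exploratory, with false-discovery-rate or cluster-based permutation control.
- State which comparisons the Bonferroni step covers, and at which visits EEG is recorded.
- Reconcile the two electrode counts, 19 and 15.
- Describe the outcome as band power, not as a full assessment of thalamocortical dysrhythmia, unless low-to-high-frequency coupling is also computed from the resting recording.

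The cost is a change of wording and modest extra analysis, with no new data. Fewer single-site results will be called significant.
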